### **8.3.1.2 Ancillary study (Immunohistochemistry)**

If patient agree to participate to the ancillary studies, a double labelling of Th1, Th2, Th17, Follicular helper T cells will be performed at 3 different time point:

- Screening
- Visit 5 (3 Months)
- Visit 12 (6 Months)

- If archival tissue samples from metastasis or initial tumor is available and sufficient to performed 6 X 4 $\mu\text{m}$  thick, unstained sections, no new biopsy is required at screening.

- If no archival tissue samples is available a new biopsy will be required at screening with the same procedure described above in the **“Fresh biopsy tissue samples” part.**

For visit 5 and 12 a new biopsy will be required in order to have enough tissue to performed a minimum of 6 X 4 $\mu\text{m}$  unstained section from FFPE block.

Double IHC procedures will be performed once validated by a pathologist. If double staining cannot be appropriately validated, single stains as those for the main study will be performed.

### **8.3.1.3 Tissues Samples shipment**

In case of tissue limiting, we will prioritize Exome analysis and RNA-seq first, then we will address PD1, PDL1 and CD8 expression by IHC and finally we will use material to performed double staining IHC, which we estimate less important. The tumour specimen submitted to establish eligibility should be of sufficient quantity (i.e. >100 tumour cells) to allow for PD-L1 immunohistochemistry analyses.

The following fields of data should be collected from the site/institution collecting and if, indicated shipping of the samples:

- Patient identifier (ecode or unique identifier)
- Specimen identifier (written on the specimen)
- Site identifier
- Specimen collection date
- Type of specimen submitted
- Quantity of specimen
- Date of sectioning

- Archival or fresh tumor and localization (initial tumor or metastasis)
- Tumor type
- Primary tumor location
- Metastatic tumor location (if applicable)
- Fixative

**The following fields of data should be collected from PD-L1 testing laboratory:**

- Are the negative and positive controls stained correctly
- Is the H&E material acceptable
- Is morphology acceptable
- Total percent positivity of PD-L1 in tumor cells
- PD-L1 status (positive, negative or NA) in tumor cells

Total percent positivity of PD-L1 in infiltrating immune.

Samples will be send at the end of the study by a shipment organized by the sponsor.

#### **8.3.1.4 Summary of tissue sample management**

| Whole exome analysis and RNAseq |                                                                                                                                                                                                                      |
|----------------------------------------|----------------------------------------------------------------------------------------------------------------------------------------------------------------------------------------------------------------------|
| Screening                       | Archival tissue samples (initial tumor or metastasis)                                                                                                                                                                |
|                                        | - 10 X 5 µm thick, unstained sections from FFPE block
- 1 HES blade encircling the tumor zone and an estimate of the tumor cell content of the fringed area                                                       |
|                                        | Fresh biopsie (metastasis)                                                                                                                                                                                           |
|                                        | 2 core fresh biopsy fixed in formalin and paraffin
- 10 X 5 µm thick, unstained sections from FFPE block
- 1 HES blade encircling the tumor zone and an estimate of the tumor cell content of the fringed area |
| Condition of sending            | Send at room temperature throughout the study or one single sending at 4°C at the end of the study                                                                                                                   |
| Shipment adress                 | Centre Georges-François Leclerc
Plateforme de transfert en biologie cancérologie
Etude Medi-Treme-Colon - [name]
[name]                                                   |

| Immunohistochemistry        |                             |                                                                                                                                                                    |
|-----------------------------|-----------------------------|--------------------------------------------------------------------------------------------------------------------------------------------------------------------|
| Principal study             | Screening                   | Archival tissue sample (initial tumor or metastasis)                                                                                                        |
|                             |                             | 5 to 11 X 4 µm thick, unstained sections from FFPE block                                                                                                           |
|                             |                             | Fresh tissue sample (initial tumor or metastasis)                                                                                                           |
|                             |                             | 5 to 11 X 4 µm thick, unstained sections from FFPE block                                                                                                           |
| Ancillary study             | Screening                   | Archival tissue sample                                                                                                                                      |
|                             |                             | 6 X 4µm thick, unstained sections from FFPE block                                                                                                                  |
|                             |                             | Fresh tissue sample (metastasis)                                                                                                                            |
|                             |                             | 1 core fresh biopsy fixed in formalin and paraffin
6 X 4µm thick, unstained sections from FFPE block                                                            |
|                             | Visit 5 Day 1
(3 Month)  | 1 core fresh biopsy fixed in formalin and paraffin
6 X 4µm thick, unstained sections from FFPE block                                                            |
|                             | Visit 12 Day 1
(6 Month) | 1 core fresh biopsy fixed in formalin and paraffin
6 X 4µm thick, unstained sections from FFPE block                                                            |
| Condition of sending |                             | Send at room temperature throughout the study or one single sending at 4°C at the end of the study                                                                 |
| Shipment adress      |                             | Centre Georges-François Leclerc
Plateforme de transfert en biologie cancérologie
Etude Medi-Treme-Colon - [name]
[name] |

|                     | Summary of tissue samples required at screening |                               |
|---------------------|-------------------------------------------------|-------------------------------|
|                     | Principal study                                 | Principal + ancillary study   |
| Exome analysis      | 10 X 5µm + 11 X 4µm                             | 10 X 5µm + 11 X 4µm + 6 X 4µm |
| IHC principal study |                                                 |                               |
| IHC ancillary study |                                                 |                               |

Table 6. Summary of Biopsy tissues samples

### 8.3.2. Immunomonitoring study (Ancillary study):

In total, four blood sampling time will be required to study the immune response analysis:

- At the inclusion, before first treatment is administrated (Cycle 1 day1) (Day 0)
- At Visit 2 (Cycle 2 day 1 before treatment of Cycle 2 is administrated), (Day 15)
- At Visit 5 (Cycle 5 day 1 before treatment of Cycle 5 is administrated), (Day 90)
- At Visit 12 (Cycle 12 day1 before treatment of Cycle 12 is administrated), (Day 180), unless progression diseases occur before C12, in that case samples will require to be collected at the end of treatment visit.

\* At each time point, the following samples will be collected:

- 7 EDTA tubes (Purple cap) - 6mL: in total 42 mL
- 2 Heparin tubes (Without gel, dark green cap) - 6mL: in total 12 mL
- 1 dry tube (without gel, red cap) - 6mL: in total 6 mL

Each sample should be identified with the following informations:

- name of the study
- identification number of the site
- inclusion number of the patient
- ⊖ name of the Visit (Visit 1/Visit 2/Visit5/Visit 12 or EOT)
- date and time of collection / name of the study.

● **6 EDTA tubes:** As soon as the 6 tubes are collected, homogenize the tubes by about 10 aversions. Label the tubes with the patient's anonymization number, the type of visit and the date of the visit. The samples will be sending by a carrier dedicated to the study. Samples must be sent within 24 hours to the central laboratory "The biomonitoring platform CIC1431 – Hôpital Jean-Minjoz, [name] " Be careful, the sampling must be done in the morning in order to be removed in the afternoon. The carrier must be informed the day before the pick-up. No removal can be scheduled on Friday or the day before a public holiday.

Samples will be used to:

- Analyze cytokine production by T cells: Th1 cytokines (IFN- $\gamma$ , IL-2, TNF), Th2 (IL-4, IL-5, IL-13), Th17 (IL17A), Treg (IL-10, TGF) and inflammatory (IL-1, IL-6, IL 15) must be measured in serum samples on PBMC after stimulation with TCR triggering by Luminex (Biorad) technology.
- study evaluation of lymphocyte reactivity to tumor antigens. The reactivity of the hTERT-specific T cells and other tumor antigens will be tested by ELISpot, by proliferation and by ELISA. A pool of 32 peptides containing pan-HLA derived EBV, CMV viral proteins and influenza (CEF Peptide Pool "Plus" set; CTL Europe GmbH) used as positive control.

Those parts would be realized by the bio-monitoring platform from the CHU of Besançon (CIC1431), under the direction of [name].

● **1 EDTA tubes** will be used for complete blood count. Each local laboratory procedures will be used for this part, as it is a routine exam. Volume of the tube will depend on local practice (4 or 6 mL)

● **2 HEPARINE:** As soon as the 2 tubes are collected, homogenize the tubes by about 10 aversions. Label the tubes with the patient's anonymization number, the type of visit and the date of the visit. The samples will be send by a carrier dedicated to the study. Samples must be sent within 24 hours to [name] at the "plateforme de transfert en biologie cancérologie" from the centre Georges-François Leclerc, [name]. Be careful, the sampling must be done in the morning in order to be removed in the afternoon. The carrier must be informed the day before the pick-up. No removal can be scheduled on Friday or the day before a public holiday.

Samples will be used to study, by multiparameter flow cytometry, the phenotype of lymphocyte subpopulations in peripheral blood. The following markers will be tested:

- Activation markers : CD45RA, CD45RO, HLA-DR, CD28, 4-1BB, (on CD8 and CD4 T cells),
- Anergy markers: PD1, BTLA, TIM-3, CTLA-4 (on CD8 and CD4 T cells),
- Immunostaining regulatory T cells: CD3, CD4, CD25, CD127, FoxP3,
- Immunostaining NK cells: CD3, CD56, NKp30, NKp44, NKp46, NKG2D, CD16, CD69, CD86, HLA-DR.

- Immunostaining of PD-L1 expressed by cells in blood.
- MDSC: CD33, HLA-DR, CD14, CD15, Lin-.

● **1 Dry tube** (without gel): As soon as the tube is collected, homogenize the tube by about 10 aversions. Then the tube should be leave at room temperature 30 minutes to allow clotting to take place. The tube should then be centrifuge 10 minutes at 1500g at 20-25°C. The serum will then be split in 3-4 tubes containing 1 mL of serum. Samples should then be stored at -80°C and will be send to the “plateforme de transfer ten biologie cancérologie” at the end of the study.

Serum will allow to performed circulating PD-L1 analysis. Circulated PD-L1 evaluated by ELISA. This part will be realized by CRI INSERM in Dijon, under the direction of [name].

|                              | PBMC                                                                                                                   | NFS                                           | Whole exome analysis                                                                                                       | Immuno-phenotyping                          | Serum library                                                                                                                        | Total blood volume |
|------------------------------|------------------------------------------------------------------------------------------------------------------------|-----------------------------------------------|----------------------------------------------------------------------------------------------------------------------------|---------------------------------------------|--------------------------------------------------------------------------------------------------------------------------------------|--------------------|
| C1J1                  | X 6 EDTA
6mL
(purple cap)                                                                                 | X 1 EDTA
6mL or 4mL
(purple cap) | X 1 EDTA
6mL
purple cap                                                                                       | X 2 HEPARIN
6mL
dark green cap | X 1 Dry tube
6mL
red cap                                                                                                | 66 ml              |
| C2J1                  | X 6 EDTA
6mL
purple cap                                                                                   | X 1 EDTA
6mL or 4mL
purple cap   |                                                                                                                            | X 2 HEPARIN
6mL
dark green cap | X 1 Dry tube
6mL
red cap                                                                                                | 60ml               |
| C5J1                  | X 6 EDTA
6mL
purple cap                                                                                   | X 1 EDTA
6mL or 4mL
purple cap   |                                                                                                                            | X 2 HEPARIN
6mL
dark green cap | X 1 Dry tube
6mL
red cap                                                                                                | 60ml               |
| C12J1                 | X 6 EDTA
6mL
purple cap                                                                                   | X 1 EDTA
6mL or 4mL
purple cap   |                                                                                                                            | X 2 HEPARIN
6mL
dark green cap | X 1 Dry tube
6mL
red cap                                                                                                | 60ml               |
| Condition for sending | room temperature within 24h                                                                                            | NA                                            | room temperature within 24h                                                                                                |                                             | at the end of the study within dry ice                                                                                               |                    |
| Shipment Adress       | The biomonitoring platform
CIC1431 – Hôpital
Jean-Minjoz,
[name] | Local analysis                                | plateforme de transfert en biologie
cancérologie
centre Georges-François Leclerc, [name] |                                             | plateforme de
transfert en biologie
cancérologie
centre Georges-
François Leclerc, [name] |                    |

**Table 7. Volume of Blood to be drawn From Each Subject**

### 8.3.3. Withdrawal of informed consent for donated biological samples

If a subject withdraws consent to the use of donated samples, the samples will be disposed of/destroyed, and the action documented. As collection of the biological samples is an integral part of the study, then the subject is withdrawn from further study participation.

The Principal Investigator:

- Ensures that biological samples from that subject, if stored at the study site, are immediately identified, disposed of /destroyed, and the action documented
- Ensures the laboratory(ies) holding the samples is/are informed about the withdrawn consent immediately and that samples are disposed/destroyed, the action documented and the signed document returned to the study site
- Ensures that the subject is informed about the sample disposal.

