### **4.3 Withdrawal of Subjects from Study Treatment and/or Study**

An individual subject will not receive any further Durvalumab or Tremelimumab products if any of the following occur in the subject in question:

- 1. Withdrawal of consent or lost to follow-up
- 2. Adverse event that, in the opinion of the investigator or the sponsor, contraindicates further dosing
- 3. Subject is determined to have met one or more of the exclusion criteria for study participation at study entry and continuing investigational therapy might constitute a safety risk
- 4. Pregnancy or intent to become pregnant
- 5. Any AE that meets criteria for discontinuation
- 6. Dose-limiting toxicity
- 7. Grade ≥ 3 infusion reaction
- 8. Subject noncompliance that, in the opinion of the investigator or sponsor, warrants withdrawal; eg, refusal to adhere to scheduled visits
- 9. Initiation of alternative anticancer therapy including another investigational agent
- 10. Confirmation of PD and investigator determination that the subject is no longer benefiting from treatment with durvalumab

Subjects who are permanently discontinued from further receipt of investigational product, regardless of the reason (withdrawal of consent, due to an AE, other), will be identified as having permanently discontinued treatment.

Subjects who are permanently discontinued from receiving investigational product will be followed for safety per Section 10.0 unless consent is withdrawn or the subject is lost to follow-up or enrolled in another clinical study, in these cases, all study procedure will be stopped. All subjects will be followed for survival. Subjects who decline to return to the site for evaluations will be offered follow-up by phone every 4 months as an alternative.

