#### **Withdrawal of consent**

If consent is withdrawn, the subject will not receive any further investigational product or further study observation.

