### **8.1.3 End of Treatment**

End of treatment is defined as the last planned dosing visit within the 24-month dosing period corresponding to Cycle 48. For subjects who discontinue durvalumab or tremelimumab prior to 12 months, end of treatment is considered the last visit where the decision is made to discontinue treatment. All required procedures may be completed within  $\pm 7$  days of the end of treatment visit. Repeat disease assessment is not required if performed within 28 days prior to the end of treatment visit.

Procedures to be conducted at the end of treatment visit are listed below:

- Complete physical exam
- ECOG Performance Status
- Vitals signs, weight
- 12-lead ECG
- Review of prior/concomitant medications
- Imaging by CT scan
- Clinical laboratory tests scheduled as described in the schedule of assessment:
  - Hematology (see Table 3)
  - Clinical chemistry (see Table 4)
  - TSH

- Coagulation (PT, PTT, INR)
- Creatinine Clearance
- Serum pregnancy test (for women of childbearing potential only) if clinically indicated
- Hepatitis serologies
- Urinalysis (see Table 5)

All subjects will be followed for survival until the end of the study regardless of further treatments, or until the sponsor ends the study.

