## **12.3. Informed consent**

Prior to the implementation of the biomedical research on a person, subject should be fully informed by the investigator during the consultation and after a period of reflection sufficient written informed consent form should be collected.

The information for the trial participants should include all elements defined in the Public Health Act of August 9, 2004 and must be written in a simple and understandable language for the patient.

The consent form must be dated and signed personally by the research participant and investigator (original archived by the investigator, a copy will be given to the research participant).

In the case of research aimed to carry out analyzes of genomics or proteomics, the informed consent form should specify the type of research to be conducted and the patient must have the ability to accept or decline conservation of biological samples for a scientific research purposes.

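### Section 8.3.3 removes from the study anyone who revokes even an optional sample consent, and section 4.3 stops tumour assessment on entry to another study that sections 9.1 and 9.4 continue

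*Protocol*

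**What the plan says.** **Sample consent.** Section 8.3.3 stands level with the principal and ancillary sampling sections (8.3.1 and 8.3.2) and directly follows the ancillary blood sampling. Its trigger is general: "If a subject withdraws consent to the use of donated samples, the samples will be disposed of/destroyed, and the action documented". Its consequence is: "As collection of the biological samples is an integral part of the study, then the subject is withdrawn from further study participation".

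Elsewhere much of the sampling is optional. Section 8.1.4 gives the exploratory study its own consent form. Section 8.3.1.2 makes the serial biopsies conditional: "If patient agree to participate to the ancillary studies". Note n to the exploratory schedule (Figure 2) ties the genetic blood sample to a signed genetic consent form. For genomic and proteomic research, section 12.3 adds that "the patient must have the ability to accept or decline conservation of biological samples for a scientific research purposes". The sample consent that section 4.1 requires for entry to the principal study is agreement to use archived tissue (criterion 12).

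**Another study.** Section 4.3 covers subjects already permanently off investigational product. It exempts from safety follow-up those who withdraw consent, are lost, or are "enrolled in another clinical study, in these cases, all study procedure will be stopped. All subjects will be followed for survival". Section 8.1.3 says: "All subjects will be followed for survival until the end of the study regardless of further treatments, or until the sponsor ends the study". Section 9.1 schedules scans until progression is documented, and section 9.4 keeps tumour assessments going in patients taken off durvalumab plus tremelimumab for anything other than confirmed progression.

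**The concern.** The phase II primary objective is progression-free survival in MSS patients, and the primary decision uses a 3-month evaluation. Both depend on tumour assessment continuing until progression. Two rules interrupt it in patients who may not have progressed.

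The first treats two patients with the same current consent differently. One never agreed to optional sampling and is scanned on schedule. The other agreed, later changed their mind, and must leave. Nothing about the need for PFS data distinguishes them.

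The second gives a site two instructions for the same patient: stop every procedure because the patient has entered another study, and continue tumour assessment because treatment ended without confirmed progression. Sites could resolve this differently.

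In a single-arm trial no control group shows whether patients lost in this way differ from those who stay.

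**Working it through.** No stated figure carries this point, so the check sets the sections side by side.

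**A. Section 8.3.3 applied to four patients**

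1. *Never joins the ancillary study.* Sections 8.1.4 and 8.3.1.2 allow this. Treatment, scans and follow-up run as scheduled.
2. *Joins, then revokes ancillary consent before the first on-treatment scan* (cycle 6; sections 8.1.2 and 9.1). Section 8.3.3 removes the patient from participation, so the scan is not done under the protocol. Sections 11.2.2 and 11.3.2 admit to the modified intention-to-treat set only patients with a 3-month evaluation, so this patient falls outside it. The repeat analysis in all enrolled patients still counts the patient, but without that evaluation.
3. *Joins, then revokes after the 3-month evaluation.* The primary evaluation exists. Later scans stop, so a later progression date is not collected under the protocol.
4. *Withdraws consent to the archived tissue.* This consent is an entry criterion, and tumour tissue supplies RAS and MSI status (sections 8.1.1 and 8.3.1.1), which define eligibility and the primary MSS population. Here the description of samples as integral has a basis.

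Patients 1 and 2 end with the same consent status but different follow-up. Section 13.2, on monitoring, describes withdrawal of sample consent only as reporting, identifying and destroying the samples. It mentions no exit from the study.

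**B. Section 4.3 against the follow-up rules, for a patient off treatment without progression who enters another study**

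- Survival: 4.3 and 8.1.3 both retain it. No loss.
- Tumour assessment: 4.3 stops it; 9.1 and 9.4 continue it. Direct conflict.
- Adverse events: section 10.2.1 sets 90 days after the last dose, or until alternative anticancer therapy starts. If the other study gives such therapy, the window has already closed.
- Related SAEs until confirmed progression (10.2.1): required of patients who continue tumour assessments. The rule depends on the conflict above and adds no separate one.

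**C. Does any design figure move?**

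Inputs (sections 11.3.2, 11.3.4, 11.4): first stage 16, continue with 9 or more; final 43, success with 26 or more; 50% against 70.7% at 3 months.

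The probability of declaring success is the sum over x = 9 to 16 of b(x; 16, p) × P(Y ≥ 26 − x), with Y ~ Binomial(27, p).

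- p = 0.50: 0.093, within the 10% limit.
- p = 0.707: 0.901, meeting 90%.
- Inflation at the 20% non-evaluable share of section 11.4: 43 × 1.20 = 51.6, rounded up to 52.

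The plan's figures reproduce, and neither withdrawal rule enters them. The margin between MSS patients planned and evaluable patients needed is 52 − 43 = 9.

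**The case against.** The best defence is that little is lost. Samples are integral to the principal study; section 4.3 keeps survival follow-up; its procedures clause can be read as a deliberate exception to 9.4; and non-evaluable patients are allowed for. Much of this stands, and it rules out several stronger readings a reader might infer.

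- *That both rules end all observation.* They do not. The wording "If consent is withdrawn, the subject will not receive any further investigational product or further study observation" belongs to general withdrawal of consent. Section 8.3.3 speaks of participation, and 4.3 retains survival.
- *That these exits are unrelated to the disease, or are demonstrably informative.* Neither is shown. Entry to another study may follow progression, when the PFS event is already recorded.
- *That section 4.3 loses the 90-day safety data.* The window already ends at alternative anticancer therapy, so for the ordinary case of a new cancer trial nothing more is removed.
- *That refusing a biopsy or blood draw triggers 8.3.3.* The trigger is withdrawing consent to the use of donated samples. The burden of sampling therefore does not show how often the rule would apply.
- *That each lost patient costs 1/43 = 2.3 percentage points.* The primary set is the first 43 evaluable patients. A patient without the evaluation is not in that denominator.
- *That section 12.3 alone forbids the rule.* It concerns keeping samples in genomic and proteomic research, so it is supporting context.

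The defence does not remove the two text conflicts. Section 8.3.3 makes no distinction between required and optional samples, and if 4.3 is meant as an exception to 9.1 and 9.4, none of these sections says so.

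**Conclusion.** The point holds as two wording conflicts that affect tumour follow-up. As written, section 8.3.3 removes a patient who revokes only an optional consent, which is inconsistent with the optional status of those samples. Section 4.3 is unreconciled with 9.1 and 9.4 for patients who enter another study without progression.

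The size is limited. The documents give no rate for either event, so the number of patients affected cannot be estimated. No sample size, power or error rate changes. The consequences are missing progression dates and, for exits before the 3-month evaluation, absence from the primary analysis set. The first conclusion assumes that sites apply 8.3.3 literally; the second, that the patient has not yet progressed. The correction should be made because it is cheap and protects the primary endpoint's data.

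**What to change.** **Section 8.3.3.** Name the samples covered. For optional ancillary, exploratory or genetic samples, limit the consequence to destroying those samples and ending ancillary sampling. State that PFS, OS and adverse event collection continue unless the patient separately withdraws consent to follow-up. Any consequence for study treatment must be reconciled with 8.1.4, 8.3.1.2 and 12.3; which treatment rule applies is for the sponsor to settle.

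**Section 4.3.** Reconcile with 8.1.3, 9.1 and 9.4. State that, for patients who enter another study without progression, vital status and the date of progression (from routine scans) are still recorded. Leave the adverse event window as section 10.2.1 defines it.

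**Cost.** An amendment and matching consent-form wording. Sites would retrieve progression date and vital status from the medical record for a few patients. No recalculation is needed.
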